Patient decision aids are interventions that can inform appropriateness criteria for TKA, potentially improving the quality of decisions about appropriate use by supporting shared decision-making between patients and their providers. [11, 12] Patient decision aids in total joint arthroplasty have been found to: increase patient knowledge, result in more realistic expectations, [12, 13] improve patient/provider communication, [14] result in fewer patients having surgery, [12, 13, 15] and be a cost-effective use of resources. [16] While the role of patient decision aids in TKA is promising, there are limitations. Notably, previously developed decision aids are not individualised for each patient, instead relying on average risk information. In addition, they tend to provide information on a narrow set of clinically focussed outcomes (e.g., operative mortality) but not on how treatment will influence outcomes such as pain, which is a clear priority for patients, [17] in addition to mobility, ability to self-care, and ability to participate in activities of daily living [18].

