HRQoL will be assessed by the EQ-5D-5L instrument, [27] which is a generic instrument that has been demonstrated to be valid and reliable in arthritis patients, [29] and the condition-specific Western Ontario and McMaster Osteoarthritis Index (WOMAC) instrument. [30] The WOMAC is widely used to evaluate changes in quality-of-life for people with osteoarthritis, and specifically for those undergoing TKA. It includes three subdomains related to pain, stiffness, and physical functioning, and has been shown to be reliable and valid in a variety of patient groups and across a range of interventions. [31] Depression at baseline will be assessed by the Patient Health Questionnaire (PHQ-9). Treatment preference will be elicited based on a question from the appropriateness checklist which asks whether the patient feels the potential benefits of surgery outweigh the potential surgical harms. [4] We will also include the SURE measure of decisional conflict, which includes four additional items that measure personal perceptions of uncertainty in choosing options, factors contributing to uncertainty, and effective decision-making. SURE been shown to be both internally consistent and reliable (test-retest exceeded 0.78), is correlated with the constructs of knowledge, regret and discontinuance, and has the ability to discriminate between those who make and delay decisions. [32] Willingness to have surgery will be assessed using a single item question.

Preference for involvement in decision-making will be assessed by the Control Preferences Scale (CPS) which ranges from “I prefer to make the final treatment decision” to “I prefer to leave all treatment decisions to my doctor.” [33] Patient-reported shared decision-making will be assessed using the CollaboRATE scale, a validated patient-reported measure which measures shared decision making through three brief questions. [33, 34] Decisional regret will be assessed by the 5-item decisional regret scale, [36] and patient satisfaction will be assessed using a validated three-item instrument. [37] In patients who had surgery, we will assess whether the expectations of surgery were met with a question that has been used previously in joint replacement. [7] Lastly, feasibility will be assessed based on recruitment rates, and rate of questionnaire completion pre and post surgery.

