#### Follow-up assessment (t2)

The final follow-up point (3-months post-surgery) will assess a variety of outcomes. For those who had surgery, they will be asked to complete *Routine Questionnaire 3*, while those that did not have surgery will complete *Study Questionnaire 3* at approximately 1 year from baseline (Fig. 1). Both these surveys will assess the patients’ health status (EQ-5D and WOMAC). All participants will then complete *Study Questionnaire 4* (Fig. 1), which assesses patient satisfaction, and some study-specific outcomes including: decisional regret and whether expectations were met. All data collection will be completed through online questionnaires.

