### Statistical methods (Table 2)

The primary analysis evaluating decision quality will be by intention-to-treat. There is no risk of participants in the no decision aid arm receiving the decision aid intervention. However, some participants randomized to the patient decision aid may not complete or engage with the tool in a meaningful way. This includes participants who click through the decision aid without spending sufficient time to read the material. A secondary analysis will assess decision quality while excluding those that do not engage, determined by a minimum of 20 min to complete the decision aid. We will analyze the participants who are lost-to-follow-up using multiple imputation to fully understand the uncertainty due to missing data. Secondary outcomes will be compared as described in Table 2.

**Table 2 Tab2:** Analysis of primary outcome and secondary outcomes

Outcome	Categorical (Cat) Continuous (Con)	Decision aid arm (DA)	No decision aid arm (RP)	Notes
Decision quality	Cat	DQ_2,DA_	DQ_2,RP_	
Quality of Life (Generic)	Con	E_2,DA_ – E_0,DA_	E_2,RP_ – E_0,RP_	
Quality of Life (Condition-specific)	Con	W_2,DA_ – W_0,DA_	W_2,RP_ – W_0,RP_	
Depression	Con	P_2,DA_ – P_0,DA_	P_2,RP_ – P_0,RP_	
Knowledge	Cat	K_0,DA_	K_0,RP_	Modified version of the 5-item HK-DQI
Decisional conflict	Cat	DC_0i,DA_	DC_0i,RP_	Evaluated for each question individually (i = 1–4)
Treatment preference	Cat	Pref_0,DA_	Pref_0,RP_	
Preference for involvement in decision-making	Cat	CPS_0,DA_	CPS_0,RP_	
Willingness to have surgery	Cat	Will_1,DA_	Will_1,RP_	
Patient-reported shared decision-making	Cat Con	C_1,DA_	C_1,RP_	Top-score: complete SDM vs. not complete Mean-score: complete SDM (12) to no SDM (0)
Decisional regret	Con	R_2,DA_	R_2,RP_	
Satisfaction	Con	S_2,DA_	S_2,RP_	Only for those who had surgery
Expectations	Cat	EXP_2,DA_	EXP_2,RP_	Only for those who had surgery
Surgical consult	Cat	Consult_1,DA_	Consult_1,RP_	
Surgery	Cat	Surg_2,DA_	Surg_2,RP_	
Concordance	Cat	Con_2,DA_	Con_2,RP_	
Feasibility: Recruitment	Con	Recruit_0,DA + RP_		Evaluated for the trial and reported as a percentage
Feasibility: Questionnaire Completion	Con	Complete_0,1,2,DA + RP_		Evaluated for the trial and reported as a percentage

HK-DQI: Hip and Knee Decision Quality Instrument; SDM: Shared Decision Making

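### Satisfaction and expectations met are tested between arms only in operated patients, a group formed after randomisation that the decision aid may alter, so neither test is a randomised comparison

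*Protocol article*

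**What the plan says.** All references are to the protocol article.

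- **Statistical methods, Table 2.** Satisfaction (S_2, continuous) and expectations (EXP_2, categorical) are set out as aid arm against control arm, each with the note "Only for those who had surgery". The text states "Secondary outcomes will be compared as described in Table 2". Continuous outcomes get a two-sample t-test; categorical outcomes get a Cochran-Mantel-Haenszel test with a relative risk. Regression adjustment is planned only if covariates such as age or sex are imbalanced.
- **Statistical methods, analysis principle.** "The primary analysis evaluating decision quality will be by intention-to-treat". No such statement is made for the secondary outcomes.
- **Table 2, surgery row.** Surgery (Surg_2) is itself compared between arms.
- **Background.** Earlier decision aids in total joint arthroplasty have been found to "result in fewer patients having surgery".
- **Secondary outcomes.** "patient satisfaction will be assessed using a validated three-item instrument", with no restriction to operated patients. The expectations item is restricted: "In patients who had surgery, we will assess whether the expectations of surgery were met".
- **Follow-up assessment (t2).** "All participants will then complete" Study Questionnaire 4, "which assesses patient satisfaction, and some study-specific outcomes including: decisional regret and whether expectations were met". Operated patients are assessed 3 months after surgery, the others about 1 year from baseline.

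**The concern.** Randomisation balances everyone who enters the trial. It does not balance those who later have surgery if the intervention influences that decision, and influencing the decision is the purpose of the aid. If the aid steers away patients who would have been disappointed with surgery, the operated patients in that arm will look more satisfied although no one's surgical result has changed. The reverse selection would make the aid look harmful. Equal surgery rates would not settle the matter, because different kinds of patients could be operated on in each arm.

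The link to these two outcomes is plausible on the article's own account: the Background calls pre-operative expectations the strongest predictor of satisfaction, and the aid is meant to change expectations. Adjustment for age or sex does not reach that mechanism, and the limitations in the Discussion do not mention it. The risk is that a difference in satisfaction among operated patients is reported as an effect of the aid when it reflects only who was operated on.

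**Working it through.** **Plan figures.** The article gives no figure for satisfaction or expectations. The only one used here is the 127 per arm for the primary outcome, as the approximate number followed up. It reproduces with the pooled two-proportion formula at 44.5% against 62%, two-sided 5%, 80% power:

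n = [1.960 × √(2 × 0.5325 × 0.4675) + 0.842 × √(0.445 × 0.555 + 0.62 × 0.38)]² / 0.175² ≈ 126.4, rounded up to 127.

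That figure is not in dispute.

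**Passages side by side.**

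| Outcome | Secondary outcomes text | Follow-up text | Table 2 |
|---|---|---|---|
| Satisfaction | no restriction | Study Questionnaire 4, all participants | operated only |
| Expectations met | operated only | Study Questionnaire 4, all participants | operated only |
| Decisional regret | no restriction | Study Questionnaire 4, all participants | no restriction |

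For satisfaction, Table 2 is narrower than both text passages. For expectations, Table 2 agrees with the outcome definition, and it is the follow-up wording that is loose.

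**Illustration of selection alone.** Suppose the aid changes no patient's satisfaction after surgery and only deters some patients from having it. Satisfaction is treated as yes/no for simplicity, although Table 2 lists it as continuous.

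- Satisfied among operated controls: 80%, from the Background's figure of up to one in five dissatisfied.
- s0, control surgery rate: assumed 70 to 90%.
- d, fall in surgery rate with the aid: assumed 5 to 15 points.
- q, proportion of deterred patients who would have been satisfied: assumed 40 to 80%.

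Satisfied among operated patients in the aid arm = (0.80 × s0 − q × d) / (s0 − d).

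Spurious difference = d × (0.80 − q) / (s0 − d).

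| s0 | d | q | Aid arm | Difference |
|---|---|---|---|---|
| 80% | 10 | 80% | 80.0% | 0 |
| 80% | 10 | 60% | (0.64 − 0.06)/0.70 = 82.9% | +2.9 points |
| 80% | 10 | 50% | (0.64 − 0.05)/0.70 = 84.3% | +4.3 points |
| 80% | 10 | 40% | (0.64 − 0.04)/0.70 = 85.7% | +5.7 points |
| 70% | 15 | 40% | (0.56 − 0.06)/0.55 = 90.9% | +10.9 points |

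Over the full assumed ranges the difference runs from 0 to +10.9 points. Its sign is the sign of 0.80 − q, so it would be negative if deterred patients would have been more satisfied than the rest.

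**Against sampling error.** With 127 followed per arm, s0 = 80% and d = 10 points, about 102 and 89 patients are operated. At q = 60% the standard error of the difference is √(0.80 × 0.20/102 + 0.829 × 0.171/89) ≈ 5.6 points. A shift of 2.9 points is about half a standard error, and 5.7 points about one.

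**The case against.** Four points can be made for the plan.

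1. **Expectations are defined only for operated patients.** Whether expectations of surgery were met has no meaning without surgery, and Table 2 agrees with the outcome definition. A reader might infer that the restriction contradicts the collection plan for both outcomes. It does not: a questionnaire sent to everyone need not put every item to everyone. This stands.
2. **The satisfaction items are not shown.** They may ask about satisfaction with surgery. Table 1 gives satisfaction the same source (reference 7) as the expectations item, while the outcome text cites reference 37, so the wording cannot be settled from the article. A comparison of all participants would also mix assessment times. A reader might infer that satisfaction must be tested in everyone randomised; that holds only if the items can be answered without surgery. This stands as a condition.
3. **Bias is possible, not shown.** The Background reports what earlier aids did; the article states no hypothesis that surgery will fall in this trial. A reader might infer that the comparisons are biased in favour of the aid. The article supports neither a size nor a direction, and the illustration depends on assumed rates. This stands.
4. **The stakes are limited.** These are two secondary outcomes in a trial of preliminary effectiveness, the operated-only population is openly stated, and regret is compared without restriction. This stands.

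None of this makes the operated groups comparable. Even where the restriction follows from the construct, a formal test between arms in a group formed after randomisation does not estimate a randomised effect, and the article neither says so nor guards against it. The choice is fixed in the article's own analysis table, so it is not a detail left to an analysis plan that is not shown.

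**Conclusion.** The point holds in a limited form. The planned tests of satisfaction and expectations met among operated patients are open to selection bias of unknown size and direction, and cannot be read as randomised effects of the aid. Under the stated assumptions, selection alone gives between 0 and about 11 points in the proportion satisfied. It gives 0 if deterred patients would have answered like the rest, and there would be no bias at all if the aid left unchanged who is operated on. The upper end needs a low control surgery rate, a large fall in surgery and much lower satisfaction among the deterred, all together.

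The inconsistency between Table 2 and the text concerns who is analysed for satisfaction. For expectations, only the follow-up wording needs clarifying. The restriction touches neither the primary outcome nor the sample size nor the comparison of decisional regret.

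**What to change.** 1. In Table 2 and the statistical methods, present satisfaction and expectations met among operated patients descriptively by arm, with no p-value, labelled as not a randomised comparison. Show the number operated in each arm alongside.
2. For satisfaction, reconcile Table 2 with the secondary outcomes and follow-up sections. If the items can be answered without surgery, make the comparison in all randomised participants the between-arm analysis, and state that assessment falls 3 months after surgery for some and about 1 year from baseline for others. If they cannot, say so and keep satisfaction descriptive.
3. Keep expectations limited to operated patients, and clarify in the follow-up section that this item of Study Questionnaire 4 applies only to them.
4. Add the selection issue to the limitations.

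The cost is two table notes and a few sentences, plus a check of the satisfaction items. No new data are needed. What is given up is a formal test of each outcome among operated patients. If satisfaction is compared in everyone, the result mixes two assessment times and must be read with that in mind.

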### Outcomes

#### Primary outcome

The primary outcome for this trial is the difference in the proportion of participants making quality decisions between the two arms. Decision quality is determined to be the key outcome for establishing the effectiveness of decision-making interventions, [11] and is defined as “the extent to which patients are informed and receive treatments that reflect their goals and treatment preferences.” [28] A quality decision requires the patient to: a) be knowledgeable, and b) make a decision that is in concordance with their values. [28] Concordance requires that the patients’ values match with the decision that was implemented, defined as whether the patient had surgery or not at the final assessment. To measure knowledge, we modified one question from the 5-item Hip and Knee Decision Quality Instrument (HK-DQI) related to pain when walking after surgery. In the HK-DQI this question reads, “If 100 people have hip/knee replacement surgery, about how many will have less hip/knee pain when walking after the surgery?” Given the overlap with the EQ-5D-5L dimension of pain or discomfort, and that the decision aid provides tailored estimates of outcomes based on clinical and demographic factors, this question was modified to, “If 100 people like you have knee replacement surgery, how many people improve and have NO or SLIGHT pain or discomfort after surgery?” Individuals getting three or more correct responses (out of five) are considered knowledgeable. Concordance will require that the patient’s treatment preference match their chosen treatment. The following question will measure treatment preference: “Do you feel the potential benefits of knee replacement surgery outweigh the potential surgical risks?” Response options include: “yes,” “no,” and “unsure.” Treatment choice will be ascertained through chart review.

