### Sample size and recruitment

A previous decision aid trial in hip and knee arthroplasty found that decision quality improved from 44.5 to 56.1% through the use of a patient decision aid and surgeon report. [12] We expect that the current tool will have a greater impact on decision quality through the inclusion of tailored outcome information for each participant based on data from Alberta collected over the past 3 years, rather than presenting average outcome information for all patients. A sample size of 127 participants per arm are needed, to detect an absolute improvement in decision quality of 17.5% (an increase in decision quality from 44.5 to 62%), using a two-sided t-test at the 5% level of significance with 80% power. To account for a 10% loss to follow-up, our target enrolment is 140 patients per arm for a total of sample size of 280. Participants will be recruited from the Edmonton Bone and Joint Centre until the target sample of 280 is achieved. Based on a previous trial run at this centre, [38, 39] we will aim to recruit 40 individuals per month, requiring approximately 7 months to achieve the desired sample size.

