Categorical outcomes will be compared between groups using Cochran-Mantel-Haenszel chi-squared tests, with the relative difference in proportions between the decision aid and no decision aid arms calculated as relative risks with 95% confidence intervals. If there is imbalance in covariates previously reported to be associated with surgery uptake, such as age or sex, dichotomous outcomes will be assessed using logistic regression and reported as odds ratios with 95% confidence intervals. We will check the usual statistical assumptions and transform continuous data if necessary. We will use SAS software to fit linear models and use generalized linear models where the assumptions and data distributions are not normally distributed.

Analysis of continuous outcomes will be completed with a 2-sample 2-tailed student’s t-test. As with categorical outcomes, if there is imbalance in key covariates, continuous outcomes will be assessed using linear regression, and if the assumptions do not hold, we will use generalized linear models. Feasibility targets are: a) > 70% recruitment of eligible patients completing their PROMs electronically, and b) > 90% of patients completing study questionnaires.

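### Chance baseline imbalance decides both the adjustment and the effect scale of the primary outcome, and neither scale is the absolute difference the trial is sized on

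*Protocol article*

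**What the plan says.** Four statements in the protocol article bear on the scale of the primary analysis.

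- **Primary outcome:** "The primary outcome for this trial is the difference in the proportion of participants making quality decisions between the two arms".
- **Sample size and recruitment:** the trial is sized "to detect an absolute improvement in decision quality of 17.5" percentage points, from 44.5% to 62%, "using a two-sided t-test at the 5% level of significance with 80% power". The result is 127 per arm.
- **Statistical methods, default rule:** Table 2 classes decision quality as categorical. Categorical outcomes are compared by Cochran-Mantel-Haenszel chi-squared tests, with relative risks and 95% confidence intervals. No stratifying variable is named, so I read this default as unadjusted.
- **Statistical methods, exception:** "If there is imbalance in covariates previously reported to be associated with surgery uptake, such as age or sex", then "dichotomous outcomes will be assessed using logistic regression and reported as odds ratios with 95% confidence intervals".

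The primary outcome is not exempted from the exception. Continuous outcomes have a parallel one: a t-test by default, and regression if key covariates are imbalanced.

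**The concern.** Allocation is randomised, so any baseline imbalance is chance. The sound reason to adjust is that a covariate predicts the outcome, and that can be decided before any data are seen. Here observed imbalance decides, and it changes two things at once: whether the estimate is adjusted, and which effect measure is reported.

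The rule is also loosely fixed. It does not say how much imbalance counts. The list of covariates is illustrative only. The selection criterion is association with having surgery, whereas decision quality needs adequate knowledge as well as a treatment that matches the stated preference.

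At stake is what the trial estimates. The protocol defines and powers on an absolute difference, yet would report either a relative risk or a conditional odds ratio, depending on how the randomisation fell.

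**Working it through.** **Inputs.** p0 = 0.445, p1 = 0.62, two-sided 5% level, 80% power and 127 per arm, all from Sample size and recruitment.

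**1. Reproduce the plan's figure.** Two proportions, pooled variance, no continuity correction, mean proportion (0.445 + 0.62)/2 = 0.5325:

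n = [1.960 × √(2 × 0.5325 × 0.4675) + 0.842 × √(0.445 × 0.555 + 0.62 × 0.38)]² / 0.175²

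This rounds up to 127 per arm, with power 80.2%. The stated size is thus that of a test of the absolute difference.

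**2. The planning effect on each scale.**

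| Scale | Arithmetic | Value | Place in the plan |
|---|---|---|---|
| Risk difference | 0.62 − 0.445 | 17.5 points | outcome definition and sample size |
| Relative risk | 0.62 / 0.445 | 1.39 | default analysis |
| Marginal odds ratio | (0.62/0.38) / (0.445/0.555) | 2.03 | scale used after the switch |

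**3. The odds ratio after the switch is conditional.** Covariate-adjusted logistic regression does not estimate the marginal 2.03. Take a standard normal covariate X with logit-scale effect s. Choose a and b so that the mean of expit(a + sX) is 0.445 and the mean of expit(b + sX) is 0.62. The conditional odds ratio is exp(b − a). The values of s are assumptions:

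- s = 0.5: 2.12
- s = 1.0: 2.36
- s = 1.5: 2.73

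The arm proportions are identical in all three cases.

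**4. How often chance would trigger the switch.** No criterion is given. If imbalance meant p < 0.05 on independent covariates (an assumption), the probability is 1 − 0.95^k: 5% for one, 10% for two, 14% for three and 23% for five. The text names two, age and sex.

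**5. Type I error.** Simulation under the null: 127 per arm, both arms at 44.5%, one covariate, 6,000 runs per setting, and the assumed p < 0.05 trigger.

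| Logit SD of covariate | Fixed trigger | Whichever analysis is significant |
|---|---|---|
| 0 | 5.2% | 5.4% |
| 0.5 | 5.1% | 6.5% |
| 1.0 | 4.5% | 7.1% |

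**6. The interval that is not planned.** At the planning rates, SE = √[(0.445 × 0.555 + 0.62 × 0.38)/127] = 0.0616. The 95% interval for the difference is 17.5 ± 1.96 × 6.16, about 5.4 to 29.6 points. It needs nothing beyond the two proportions and the arm sizes.

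**The case against.** Several stronger readings are tempting, and the document does not support them.

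- **Inflated type I error.** A reader might infer this from any data-dependent choice of model. A fixed imbalance trigger does not cause it (4.5% to 5.2% above). The 5.4% to 7.1% requires picking the significant analysis, which the protocol does not propose.
- **A choice made after seeing the outcome.** The trigger uses baseline covariates. The primary outcome needs surgery status at the final assessment, and the Blinding section says analysts lack follow-up data when they are unblinded after the surgeon visits. Imbalance could be judged before the primary outcome exists. What stands is that nothing fixes that timing. Knowledge and treatment preference, two of the three components of the outcome in Table 1, are collected at baseline and could be visible by arm at unblinding.
- **A wrong sample size.** It reproduces. Without covariates the three scales share one null hypothesis, so the default test addresses the hypothesis that was powered.
- **A known switching rate.** The percentages in step 4 rest on a p < 0.05 rule that the protocol does not state.

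The threshold and full covariate list may also sit in an analysis plan that is not shown, and their absence alone would be no finding. But the article is not silent: it states a rule under which imbalance changes the effect measure, and completing the list would not cure that. Finally, a reader can subtract the two proportions, so the missing risk difference is partly a reporting matter. It still leaves the defined quantity without a planned interval.

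**Conclusion.** The point holds as a fault in how the primary analysis is fixed. Chance imbalance, judged by no stated criterion, can move the primary outcome from a relative risk to a conditional odds ratio, and neither is the absolute difference that is defined and powered on. The planning effect would read as 1.39 on one branch. On the other it would read as 2.03 or, under the assumed covariate strengths, 2.12 to 2.73. With an outcome as common as this, an odds ratio of that size is easily misread as a doubling of the proportion.

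The consequence is for the estimand, for interpretation and for analytic latitude. It does not touch the sample size or, under mechanical use, the error rate. The conclusion assumes that the categorical rule governs the primary outcome, as Table 2 indicates, and that the default test is unstratified. The change is worth making because it is cheap and the present rule has no compensating advantage.

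**What to change.** - State one primary analysis, used whatever the baseline tables show. Make the risk difference in decision quality with its 95% confidence interval the primary measure, and the relative risk with its interval supportive.
- If the primary analysis is adjusted, list the covariates in advance, justify them by expected prognostic value for decision quality, and use only measurements taken before randomisation. Age and sex are candidates: Routine Questionnaire 1 includes basic demographics and precedes recruitment. Obtain the risk difference from the logistic model by marginal standardisation, and give the unadjusted test as a sensitivity analysis.
- Include baseline EQ-5D or WOMAC only once collection before randomisation is confirmed. The baseline label in Table 1 does not establish this, since knowledge and decisional conflict carry it too and are compared between arms as outcomes. The legend of Fig. 2 also lists the EQ-5D within the decision aid overview.
- Delete the imbalance trigger for both categorical and continuous outcomes.

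The cost is a rewording of Statistical methods and minor extra analysis work. The 127 per arm is unchanged, because the trial is already sized on the risk difference. The Ethics and dissemination section provides for analysis changes by amendment.

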### Assignment of interventions

Participants will be randomly assigned to either the decision aid or no decision aid arm in a 1:1 allocation using a computer-generated randomization schedule with permuted blocks of random sizes. The randomization will be conducted in Research Electronic Data Capture (REDCap) software. All participants who meet the inclusion criteria and consent to participate will be randomized.

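### EQ-5D and WOMAC are compared by default with unadjusted t-tests on change scores; prespecified adjustment for the baseline score, already collected, would be at least as precise in large samples

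*Protocol article*

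**What the plan says.** All locations are in the protocol article.

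- **Quantity compared.** In Table 2 (Statistical methods), generic quality of life is E_2 minus E_0 and condition-specific quality of life is W_2 minus W_0, each computed by arm. Both are listed as continuous.
- **Default test.** The text after Table 2 says: "Analysis of continuous outcomes will be completed with a 2-sample 2-tailed" Student's t-test. No covariate enters.
- **Conditional alternative.** The next sentence says that "if there is imbalance in key covariates, continuous outcomes will be assessed using linear regression", with generalized linear models if assumptions fail. Key covariates are not listed. The only examples, age and sex, come from the paragraph on categorical outcomes, where they are covariates linked to surgery uptake.
- **Data in hand.** Table 1 schedules E_0 and W_0 at baseline and E_2 and W_2 at follow-up. The section on the follow-up assessment collects both measures from operated patients (3 months after surgery) and from non-operated patients (about 1 year from baseline).
- **Allocation.** Patients are randomised "in a 1:1 allocation using a computer-generated randomization schedule".

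No SD, correlation, target difference or power is given for either score.

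**The concern.** A change score fixes the coefficient on the baseline value at 1. Regression on the baseline estimates that coefficient from the data. Unless the true coefficient happens to be 1, the change score carries avoidable noise, and a chance difference between arms at baseline leaks into the estimated effect.

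The conditional switch to regression does not solve this. It is triggered by what the baseline table looks like, so the estimator is chosen after seeing data. When the arms look balanced, the precision gain is forgone. Nothing in the text says that the baseline score is one of the covariates that would trigger the switch or enter the model.

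At stake are wider confidence intervals than necessary on the two health-status outcomes. They are secondary, and the document makes no power claim for them.

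**Working it through.** **1. The plan's own figure.** The only sample size calculation is for the primary outcome: "an increase in decision quality from 44.5 to 62" per cent, "using a two-sided t-test at the 5% level of significance with 80% power". With p1 = 0.445, p2 = 0.62, mean 0.5325 and the pooled-variance formula for two proportions:

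n = [1.960 × √(2 × 0.5325 × 0.4675) + 0.8416 × √(0.445 × 0.555 + 0.62 × 0.38)]² / 0.175² = (1.383 + 0.585)² / 0.030625 ≈ 126.4, rounded up to 127.

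This reproduces "A sample size of 127 participants per arm are needed" (power 80.2% at 127). I use 127 per arm below only as a realistic evaluable number. Nothing here alters it.

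**2. General result.** Let s0 and s1 be the SDs at baseline and follow-up, and r their within-arm correlation.

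- Var(change) = s0² + s1² − 2·r·s0·s1
- Var(baseline-adjusted) = s1²·(1 − r²)
- Difference = s0² − 2·r·s0·s1 + r²·s1² = (s0 − r·s1)²

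A square cannot be negative, so in large samples adjustment never loses precision, whatever r and the SDs are.

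**3. Equal SDs.** The variance ratio reduces to (1 − r²) / [2(1 − r)] = (1 + r)/2.

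| r (assumed) | Variance ratio | SE reduction | Equivalent extra patients |
|---|---|---|---|
| 0.3 | 0.65 | 19.4% | 1/0.65 − 1 = 54% |
| 0.5 | 0.75 | 13.4% | 1/0.75 − 1 = 33% |
| 0.6 | 0.80 | 10.6% | 1/0.80 − 1 = 25% |

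**4. Unequal SDs.** The SE reduction is 1 − √[Var(adjusted)/Var(change)]. For example, with s1/s0 = 1.2 and r = 0.5: Var(change) = 1 + 1.44 − 1.2 = 1.24; Var(adjusted) = 1.44 × 0.75 = 1.08; √(1.08/1.24) = 0.933, a reduction of 6.7%.

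| s1/s0 | r = 0.3 | r = 0.4 | r = 0.5 | r = 0.6 | r = 0.7 | r = 0.8 |
|---|---|---|---|---|---|---|
| 0.8 | 29.1% | 26.7% | 24.4% | 22.4% | 20.8% | 20.0% |
| 1.0 | 19.4% | 16.3% | 13.4% | 10.6% | 7.8% | 5.1% |
| 1.2 | 12.7% | 9.6% | 6.7% | 4.0% | 1.7% | 0.2% |
| 1.5 | 6.7% | 4.0% | 1.8% | 0.3% | 0.1% | 2.4% |

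**5. Detectable difference.** With 127 per arm, equal SDs, two-sided 5% and 80% power, the detectable difference is (1.960 + 0.8416) × SD × √(2/127). In units of the common SD, it falls from 0.416 to 0.335 at r = 0.3, from 0.352 to 0.304 at r = 0.5, and from 0.314 to 0.281 at r = 0.6.

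**6. Chance baseline difference.** Given an observed baseline difference D between arms, the change-score estimate is shifted on average by (b − 1)·D, where b = r·s1/s0. With equal SDs and r from 0.3 to 0.6, that is −0.7·D to −0.4·D. The baseline-adjusted estimate removes this shift. Over repeated randomisations D averages to zero, so the shift is noise and not bias.

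**7. Price of adjustment.** One covariate costs one degree of freedom. At 254 evaluable patients (2 × 127) the SE rises by a factor of about √(1 + 1/250) = 1.002, or 0.2%.

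**The case against.** The best case for leaving the plan alone has five parts.

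- **The planned test is valid.** Under randomisation a two-sample t-test on change is unbiased, and its standard error already reflects chance baseline imbalance. This stands. A reader might infer that the quality-of-life comparisons are biased by regression to the mean; the documents do not support that.
- **These are secondary outcomes.** The primary outcome is a binary proportion and it alone drives the sample size. This stands and limits the importance of the point.
- **The gain cannot be quantified from the document.** This stands. A reader might take 11-19% as a property of this trial, but it rests on an assumed correlation and equal SDs. Equal SDs are open to doubt because follow-up mixes operated and non-operated patients at different times. The schedule makes a moderate correlation plausible (an average wait of 5 to 6 months, then 3 months after surgery), but does not establish it. A large mean improvement after surgery does not by itself lower a correlation. Nor can one conclude that the change score is noisier than the follow-up value alone: with equal SDs that needs a correlation below 0.5.
- **Regression is already foreseen.** Partly right. Key covariates are not enumerated, so the baseline score is not excluded, and an analysis plan that is not shown may list them. But the protocol itself makes regression conditional on observed imbalance, so the precision gain is still lost when the arms look balanced.
- **A change is not free.** The section on ethics and dissemination requires a protocol and ethics amendment for changes that affect the analysis. That is a real but small cost.

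**Conclusion.** The point holds as one about efficiency. The default analysis of EQ-5D and WOMAC sets aside information that is already collected, and the fallback does not reliably recover it. The direction of the gain is certain in large samples. Its size is not: about 11-19% of the standard error under the assumed correlations of 0.3 to 0.6 with equal SDs, and anywhere from about 0% to 29% over those correlations as the follow-up SD runs from 1.5 down to 0.8 times baseline. None of these correlations or SD ratios comes from the document.

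The change improves precision and protects against chance baseline imbalance on two secondary outcomes. The primary analysis and the 127 and 140 per arm are untouched. It is worth making because the cost is negligible and it removes a data-dependent choice of estimator for these two outcomes.

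**What to change.** In the statistical methods, replace the t-test on change for these two outcomes with a prespecified model: linear regression of E_2 on arm and E_0, and of W_2 on arm and W_0, fitted in every case regardless of observed balance. Report the adjusted mean difference between arms with its 95% CI.

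Age and sex may be added as fixed covariates, but the calculation above rests on the baseline score alone. The change-score t-test may stay as a supportive analysis. Table 2 can keep its change notation if preferred: once the baseline score is in the model, regressing the change or the follow-up score gives the same arm coefficient.

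Cost: about one degree of freedom per covariate, a sentence or two of text, and the amendment that the protocol requires for changes to the analysis. No new data and no change to conduct are needed.
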